## Abstract

**Background:**

Severe gait disturbances in idiopathic Parkinson's disease (PD) are observed in up to 80% of all patients in advanced disease stages with important impact on quality of life. There is an unmet need for further symptomatic therapeutic strategies, particularly as gait disturbances generally respond unfavourably to dopaminergic medication and conventional deep brain stimulation of the subthalamic nucleus in advanced disease stages. Recent pathophysiological research pointed to nigro-pontine networks entrained to locomotor integration. Stimulation of the pedunculopontine nucleus is currently under investigation, however, hitherto remains controversial. The substantia nigra pars reticulata (SNr) - entrained into integrative locomotor networks - is pathologically overactive in PD. High-frequent stimulation of the substantia nigra pars reticulata preferentially modulated axial symptoms and therefore is suggested as a novel therapeutic candidate target for neuromodulation of refractory gait disturbances in PD.

**Methods:**

12 patients with idiopathic Parkinson's disease and refractory gait disturbances under best individual subthalamic nucleus stimulation and dopaminergic medication will be enroled into this double-blind 2 × 2 cross-over clinical trial. The treatment consists of two different stimulation settings using *(i) *conventional stimulation of the subthalamic nucleus [STNmono] and *(ii) *combined stimulation of distant electrode contacts located in the subthalamic nucleus and caudal border zone of STN and substantia nigra pars reticulata [STN+SNr]. The primary outcome measure is the change of the cumulative 'axial score' (UPDRS II items '13-15' and UPRDS III items '27-31') at three weeks of constant stimulation in either condition. Secondary outcome measures include specific scores on freezing of gait, balance function, quality of life, non-motor symptoms, and neuropsychiatric symptoms. The aim of the present trial is to investigate the efficacy and safety of a three week constant combined stimulation on [STN+SNr] compared to [STNmono]. The results will clarify, whether stimulation on nigral contacts additional to subthalamic stimulation will improve therapeutic response of otherwise refractory gait disturbances in PD.

**Trial registration:**

The trial was registered with the clinical trials register of http://www.clinicaltrials.gov (NCT01355835)

## Background

### Refractory gait disturbances in Parkinson's disease

Severe gait disturbances in idiopathic Parkinson's disease are observed in up to 80% of the patients in advanced disease stages [1,2] with important impact on quality of life [3-5]. Therapeutic deep brain stimulation of the subthalamic nucleus (STN-DBS) as an evidence-based therapy [6-8] generally ameliorates segmental symptoms and motor fluctuations, whereas axial symptoms and in particular gait disturbances may respond unfavourably and generally aggravate in parallel with the underlying neurodegeneration [9,3,10]. In this condition, increasing intensity of high-frequent STN-DBS at 130 Hz even worsens the condition [10]. Currently, several approaches are under investigation in order to address the therapeutic need for gait disturbances refractory to dopaminergic treatment and STN-DBS. STN-DBS on lower frequencies, e.g. at 60 Hz can improve gait disturbances, however is limited by the recurrence of segmental symptoms like tremor, bradykinesia and rigidity [10]. Stimulation of the pedunculopontine area for refractory gait disturbances remains controversial at the moment [11-13], however several experimental lines of evidence demonstrated the integrative role of reciprocal brainstem circuitries including substantia nigra pars reticulata (SNr) and the pedunculopontine area [14-16]. Importantly, activity of the SNr can be modulated after implantation for conventional STN-DBS, as the caudal electrode contacts are generally located in the caudal border zone of STN and SNr [17,18].

### Simultaneous stimulation of STN and SNr with *interleaved pulses*: uncovering of a novel stimulation paradigm for refractory gait disturbances?

At present, stimulation impulses are generally delivered on single monopolar contacts polarised against the generator case or between bipolar adjacent electrode contacts. Recently, the advancement of the implantable impulse generators enabled the novel paradigm of the so-called *'interleaved pulses'*, i.e. stimulation impulses are delivered simultaneously on two different contacts in alternating order. Importantly, each of the contacts can be programmed onto specific parameters (amplitude, pulse width) at a common stimulation frequency (e.g. 125 Hz on each contact). This might allow for *(i) *optimization of the stimulation settings by minimizing side effects from current spreading to the vicinity of the STN (especially if stimulation on a second monopolar contact is necessary to achieve sufficient therapeutic effects without inducing side effects), and *(ii) *improved therapeutic efficacy by delivering the stimulation pulses more selectively on different and distant contacts, although both issues remain to be demonstrated in clinical studies.

In our center for deep brain stimulation electrodes in STN-DBS surgery are generally placed with the uppermost contact of the quadripolar electrode located in the rostral border zone of zona incerta and STN and the lowermost contact in the caudal border zone of STN and SNr. This neuroanatomic assumption is substantiated by several common intra- and postoperative findings: *(i) *efficacy of a proximal contact on segmental symptoms like rigidity or tremor and a facultative induction of dyskinesias on the respective contact (upon increasing energy delivery) indicates its localisation in the dorsolateral STN motor area; *(ii) *intraoperative single cell recordings often identify bursting STN activity followed by regular tonic discharge when the descending microelectrode is leaving STN and entering SNr [19]. The novel paradigm using *"interleaved pulses" *therefore enables simultaneous stimulation with specific parameters of both STN area and the caudal STN/SNr border zone.

### Objectives

We hypothesize that simultaneous stimulation on contacts located in both STN and caudal STN/SNr border zone [STN+SNr-DBS] improves gait disturbances compared to conventional STN-DBS delivered on a single contact located in the STN area [STNmono].

➢ To test the hypothesis that [STN+SNr-DBS] is more effective on hypokinetic gait disturbances compared to [STNmono] in a randomised double-blind cross-over three week follow-up.

➢ To evaluate the short term effects of the conditions [StimOff], [STNmono] and [STN+SNr] on hypokinetic gait disturbances.

➢ To assess the impact of combined [STN+SNr-DBS] on further specific gait and balance features including freezing of gait in particular, as well as further non-motor features of Parkinson's disease in terms of quality of life, non-motor and neuropsychiatric symptoms as secondary endpoints.

## Design and Methods

This double-blind randomised cross-over clinical trial consists of two arms. Severity of the gait disturbance will be assessed after a three week follow-up of both *(i) *conventional stimulation of the STN area [STNmono] and *(ii) *combined stimulation of the STN area and the caudal STN/SNr border zone [STN+SNr]. 12 consecutive patients will be randomised on blocks to the two treatment conditions in a 1:1 ratio and treatments will be crossed-over after three weeks of follow-up, respectively. Moreover, a baseline assessment *'off dopaminergic medication' *will be performed in order to assess short-term effects and to assure optimal stimulation parameters of the conventional STN-DBS [STNmono]. A composite 'axial score' including the major clinical and anamnestic items on gait, posture and balance function from UPDRSII (items 13-15) and UPDRS III (items 27-31) constitutes the primary outcome measure.

### Population and Recruitment

The patient population will consist of patients with refractory gait disturbances and advanced Parkinson's disease treated with STN-DBS with implanted impulse generators that allow for the delivery of *"interleaved pulses" *(ACTIVA PC, ACTIVA RC). Patients will be recruited at the Center of Neurology, Tübingen University.

### Inclusion criteria

• Written informed consent

• Age: between 18 and 80 years

• Idiopathic Parkinson's disease (according to the "British Brain Bank criteria" [20] including genetic forms and therapy with STN-DBS (ACTIVA pulse generator)

• Optimized subthalamic stimulation (refer 'treatment' section)

• Gait disturbance refractory to best individual STN-DBS (STNmono) and dopaminergic therapy: composite **'axial score' **in the best clinical [MedOn/STNmono] condition ≥ 12

• Clinical and image-guided or electrophysiological confirmation of *(i) *at least one of the two rostral contacts of the quadripolar electrode localized in the STN area.

• Dopaminergic medication constant for at least four weeks prior to study enrolment

• Implantation of the DBS electrodes at least 6 months before study enrolment

• Disease duration ≥ 5 years

### Exclusion criteria

• Cognitive impairment (Mini Mental State Exam < 25)

• Participation in other clinical trials within the past three months and during enrolment in our study

• Suicidality, Psychosis

• Other severe pathological chronic condition that might confound treatment effects or interpretation of the data

• Pregnancy

• Acute adverse effects from stimulation on contacts in the caudal STN/SNr border zone

#### Screening

Patients will be recruited at the Department for Neurodegenerative Diseases of the Center of Neurology, University of Tübingen, Germany. A neurologist will assess the eligibility of a patient according to the inclusion and exclusion criteria as detailed above.

#### Safety

##### Endpoints of safety are

• Death

• Severe symptomatic exacerbation of the pre-existing gait disturbance, defined by repetive falls (if not preexistant) due to aggravated freezing of gait or imbalance (UPDRS II, items 13-14, UPDRS III, item 30)

• Newly occurring or aggravated depressive symptoms (BDI), suicidality (BDI, item 9), impulsivity (Barrett impusivity scale), hallucinatory behaviour and psychosis (UPDRS I, item 2).

• worsening of segmental motor symptoms (UPDRS III, items 20-26) or motor fluctuations (UPDRS IV)

Information about these safety parameters is recorded in the CRF.

### Outcome measures

The primary outcome measure is defined as the difference of the composite 'axial score' including the major UPDRS II and III items of gait, balance and posture after three weeks of double-blind treatment with either *(i) *conventional [STNmono] or *(ii) *combined [STN+SNr-DBS]. The secondary efficacy variables enable a differentiated assessment of specified axial symptoms, namely freezing of gait (including provoking manoeuvres), gait velocity, clinical balance testing, neuropsychiatric symptoms, and non-motor symptoms.

### Study protocol

Clinical testings at baseline will be performed after overnight withdrawal of dopaminergic medication and after optimization of subthalamic stimulation. Follow-up examinations will be performed in the *'dopaminergic on state'*. Of note, no follow-up examinations with a single active SNr contact will be conducted as this previously failed to control for segmental symptoms like tremor, bradykinesia and rigidity [17].

Figure 1: Baseline testings will be performed *"off dopaminergic medication" *after overnight withdrawal with *(i) *[StimOff], *(ii) *[STNmono], and *(iii) *[STN+SNr]. On visits 1 and 2, we will assess the treatment effects of [STNmono] and [STN+SNr] after three weeks of constant stimulation on either setting. The order of the treatment conditions will be randomized and crossed after the first visit. Randomisation lists for the different treatment conditions are prepared by the Department of Medical Biometry.

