### Sample size calculation and statistical analysis plan

#### Primary Endpoint

The primary endpoint for the statistical evaluation of the therapy is the change in composite 'axial score'. The 'axial score' is built by 8 items from the UPDRS II and III, all 5-point rated. For the statistical evaluation the five rating points are represented by the numbers 0 to 4, which represent increasing levels of pathology. The 'axial score' will be scored by the sum of the ratings across the 8 items (range 0 to 32). As change in UPDRS scores is a common primary efficacy outcome measure in Parkinson's disease and only items of the original UPDRS are required for the definition of the primary endpoint the statistical evaluation methods should be based on the psychometric validation of the UPDRS and no own validation studies are necessary.

The primary endpoint for the statistical evaluation will be the change in 'axial score' from baseline to visit 2 (after 6 weeks). For every patient we will determine two change-scores for the two phases in the Cross-Over. By means of a paired t-test the null hypothesis of equality of the two therapies concerning the change in 'axial score' will be tested. The decision for maintaining or rejecting the null hypothesis will be made applying a two-sided test with α = 0.05. The observed effects will be described by use of means and effect sizes including the appropriate 95%-confidence intervals. The confirmatory statistical evaluation of the efficacy of the [STN+SNr-DBS] in this trial will be restricted to the primary endpoint. Only the rejection of the null hypothesis will be interpreted as statistical evidence for the efficacy of [STN+SNr-DBS].

As no comparable study is available at the moment, we defined an improvement of 4 points on the primary outcome measure 'axial score' to be clinically relevant on hypokinetic gait disturbances and assumed a standard deviation of 4.0 (effect size: 1.0). A sample size of 10 will have 80% power to detect a difference in means of 4.0 (e.g. first condition mean: 16.0 and a second condition mean of 12.0), using a paired t-test with a 0.05 two-sided significance level (sample size estimated using NQuery Advisor 7.0). To adjust for a maximum of two dropouts a total of n = 12 patients will be included in the study.

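### The primary endpoint is defined as a change from a baseline taken off medication, while both follow-up visits are on medication; the primary analysis should be fixed as the direct Visit 1 versus Visit 2 difference

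*Protocol article*

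**What the plan says.** Five places in the protocol article bear on this.

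- **Study protocol, baseline.** "Clinical testings at baseline will be performed after overnight withdrawal of dopaminergic medication and after optimization of subthalamic stimulation". The session covers three acute settings: StimOff, STNmono and STN+SNr. It is the only session that the article calls baseline.
- **Study protocol, follow-up.** "Follow-up examinations will be performed in the" on-medication state. The Treatment section keeps medication constant over the six weeks.
- **Primary Endpoint.** "The primary endpoint for the statistical evaluation will be the change in 'axial score' from baseline to visit 2 (after 6 weeks"). The next sentence reads: "For every patient we will determine two change-scores for the two phases in the Cross-Over". These two scores enter a paired t-test. The section does not say which of the three baseline scores is the reference, or whether the second change starts from baseline or from Visit 1.
- **Outcome measures.** Here the definition is another one: "The primary outcome measure is defined as the difference of the composite 'axial score' including the major UPDRS II and III items of gait", taken after three weeks on each setting. No baseline enters this definition.
- **Inclusion criteria.** An on-medication axial score exists, because eligibility requires a score "in the best clinical [MedOn/STNmono] condition ≥ 12". It is not named as the baseline for any analysis.

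The Handling of Missing Data section fills a missing primary value with the last earlier score.

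**The concern.** A change from an off-medication baseline to an on-medication visit measures drug and stimulation together. A setting that did nothing would still show an improvement equal to the drug effect. The plan treats 4 points as clinically relevant, so a drug effect of that size would reach the threshold alone. The Discussion says that a larger trial will be designed from this trial's effect size and standard deviation, so a contaminated figure could be carried forward.

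The confirmatory test is also exposed. If the two change scores are baseline to Visit 1 and Visit 1 to Visit 2, the drug effect falls in the first only. It then acts with opposite sign in the two sequences and enters the error term of a test on 12 patients.

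**Working it through.** **Inputs from the Primary Endpoint section:** difference 4.0, SD 4.0, two-sided alpha 0.05, n = 10 plus two for dropout.

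**Assumptions:** SD 4 at each session and correlation 0.5 between sessions, which gives SD of the paired difference = 4 × √(2 × (1 − 0.5)) = 4, as planned; six patients per sequence; reference = the off-medication STNmono score; off-to-on drug effect D of 0 to 8 points, the same for all patients.

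**1. The plan's own figure.** Paired t-test, noncentrality (4/4) × √n, df n − 1. At n = 10: noncentrality 3.16, power 80.3%. At n = 9: 74.8%. The stated n = 10 is reproduced. At n = 12: noncentrality 3.46, power 88.3%.

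**2. Change for one setting.** Let m be the mean on-medication STNmono score and m + D the mean baseline. The expected change is −D on STNmono and −4 − D on STN+SNr. With D = 4 these are −4 and −8, against 0 and −4 from a medication-matched baseline.

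**3. Contrast with one common baseline B.** (V_comb − B) − (V_mono − B) = V_comb − V_mono. B cancels in every patient, so the contrast stays at −4 and power at 88% for every D.

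**4. Contrast if the second change is taken from Visit 1.**

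- STNmono first: (V2 − V1) − (V1 − B) = V2 − 2V1 + B, mean (m − 4) − 2m + (m + D) = −4 + D.
- STN+SNr first: (V1 − B) − (V2 − V1) = 2V1 − B − V2, mean 2(m − 4) − (m + D) − m = −8 − D.
- Average over equal sequences: −6, whatever D is.
- Variance within a sequence: 16 × (1 + 4 + 1) + 2 × 8 × (−2 − 2 + 1) = 96 − 48 = 48.
- The sequence means lie 2 + D on either side of −6, so the variance that the paired test sees is 48 + (12/11) × (2 + D)².

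Power and type I error by simulation (200,000 trials per row, n = 12):

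| Assumed D | SD of differences | Power, change from Visit 1 | Power, common baseline or direct | Type I error, change from Visit 1 |
|---|---|---|---|---|
| 0 | 7.24 | 75% | 88% | 0.049 |
| 2 | 8.09 | 67% | 88% | 0.041 |
| 4 | 9.34 | 53% | 88% | 0.025 |
| 6 | 10.85 | 37% | 88% | 0.011 |
| 8 | 12.53 | 21% | 88% | 0.003 |

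The fall from 88% to 75% comes from referencing to Visit 1 and needs no drug effect. Only the fall below 75% comes from the medication mismatch: at D = 4, 13 points from the first cause and 22 from the second.

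**5. Carrying forward.** If Visit 1 is missing, the last earlier score may be the off-medication one. The drug part then moves that patient's Visit 1 versus Visit 2 contrast by D, in a direction set by the sequence. For one patient in 12 the mean moves by D/12, or 0.33 points at D = 4.

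**The case against.** The strongest reply is that the confirmatory comparison may be untouched. Both visits are on medication with constant dosing, and a common baseline cancels exactly. Other text favours the direct contrast: the Outcome measures definition, the abstract's placing of the outcome at three weeks in each condition, and a sample-size example given as condition means of 16.0 and 12.0 rather than changes. The off-medication session also has its own purpose: short-term effects and a check of the STN settings. All of this stands. A reader might infer that the comparison of STN+SNr with STNmono is confounded by medication; the documents do not support that.

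The drug effect is also an assumption. The abstract says that gait responds poorly to dopaminergic medication, so D may be small, and the rows for 0 and 2 points deserve as much attention as the larger ones.

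A reader might further infer that the full composite cannot be scored at baseline, since the score is described as "A composite 'axial score' including the major clinical and anamnestic items on gait, posture and balance function" and history items cannot reflect a setting tried briefly that day. No section says that those items are rated under each acute setting, so the point is not made here.

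What the reply does not remove is that the Primary Endpoint section names change from baseline, leaves the reference for the second phase open, and differs from the Outcome measures section.

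**Conclusion.** The concern holds as an endpoint definition that must be reconciled. It does not show bias in the comparison between settings.

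- **Certain from the text:** a change from the stated baseline for either setting, and any effect size built on it, contains the whole off-to-on drug effect. Its size is not given.
- **Conditional:** if the second change is taken from Visit 1, the expected contrast is −6 instead of −4, the test is conservative whenever D is above zero, and power at n = 12 is 75% to 21% for D from 0 to 8 points, against 88%. These figures rest on SD 4, correlation 0.5, equal sequences and a constant D.
- **No effect:** with one common baseline, or the direct visit difference, bias is zero and power is unchanged.
- **Smaller, also conditional:** a missing Visit 1 filled with an off-medication score puts D into that patient's contrast.

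**What to change.** 1. Reconcile the Outcome measures, Study protocol and Primary Endpoint sections: define the primary analysis as the within-patient difference between the on-medication axial scores at Visit 1 and Visit 2, and delete the wording on change from baseline and on phase change scores.
2. Keep the off-medication session for the short-term objective only, and do not report per-setting changes from it as stimulation effects.
3. State in the missing-data rule that off-medication scores are not carried forward, and say how a patient with only one on-medication visit is handled.
4. If a descriptive baseline is wanted, the on-medication eligibility score can serve, with a note that patients were selected at 12 or above, so that changes from it are subject to regression to the mean.

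The cost is wording, to be settled before unblinding. No visit or assessment is added; for item 4 the eligibility score has only to be kept in the case report form. The sample size stands, provided that 4.0 is meant as the SD of the paired difference.

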**Figure 1 F1:**
[figure not shown]
**Study design**.

### Withdrawal from the study

In case of endangerment of personal safety or lack of compliance or withdrawal of informed consent, a patient will instantly be excluded from further participation in the study.

### Sample size calculation and statistical analysis plan

#### Primary Endpoint

The primary endpoint for the statistical evaluation of the therapy is the change in composite 'axial score'. The 'axial score' is built by 8 items from the UPDRS II and III, all 5-point rated. For the statistical evaluation the five rating points are represented by the numbers 0 to 4, which represent increasing levels of pathology. The 'axial score' will be scored by the sum of the ratings across the 8 items (range 0 to 32). As change in UPDRS scores is a common primary efficacy outcome measure in Parkinson's disease and only items of the original UPDRS are required for the definition of the primary endpoint the statistical evaluation methods should be based on the psychometric validation of the UPDRS and no own validation studies are necessary.

The primary endpoint for the statistical evaluation will be the change in 'axial score' from baseline to visit 2 (after 6 weeks). For every patient we will determine two change-scores for the two phases in the Cross-Over. By means of a paired t-test the null hypothesis of equality of the two therapies concerning the change in 'axial score' will be tested. The decision for maintaining or rejecting the null hypothesis will be made applying a two-sided test with α = 0.05. The observed effects will be described by use of means and effect sizes including the appropriate 95%-confidence intervals. The confirmatory statistical evaluation of the efficacy of the [STN+SNr-DBS] in this trial will be restricted to the primary endpoint. Only the rejection of the null hypothesis will be interpreted as statistical evidence for the efficacy of [STN+SNr-DBS].

As no comparable study is available at the moment, we defined an improvement of 4 points on the primary outcome measure 'axial score' to be clinically relevant on hypokinetic gait disturbances and assumed a standard deviation of 4.0 (effect size: 1.0). A sample size of 10 will have 80% power to detect a difference in means of 4.0 (e.g. first condition mean: 16.0 and a second condition mean of 12.0), using a paired t-test with a 0.05 two-sided significance level (sample size estimated using NQuery Advisor 7.0). To adjust for a maximum of two dropouts a total of n = 12 patients will be included in the study.

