After the baseline examination, patients will be randomised to either [STNmono] or [STN+SNr] treatment and scheduled at three weeks of constant stimulation (Visit 1). After this first endpoint assessment treatment will be crossed-over and patients will be re-scheduled after further three weeks of constant stimulation for the second endpoint assessment (Visit 2). The follow-up period is - due to the current clinical evidence - sufficiently long to control adequately for carry-over effects since the endpoint assessment in the follow-up period will be scheduled only after three weeks of constant stimulation on either setting. STN-DBS in PD generally evokes clinical effects within short time intervals ranging from several seconds to few hours and presents completely reversible in the same time range. In the first patient described with improvement from [STN+SNr] compared to [STNmono], the clinical superiority of [STN+SNr] was demonstrated after 30 minutes of constant stimulation on either setting [18], and monopolar stimulation on STN or SNr contacts revealed discriminable clinical effects on segmental and axial symptoms if both settings were applied randomly within one day in an independent study [17]. Dopaminergic medication will be held constant during the whole six week cross-over period and should be stable for at least 4 weeks before study enrolment.

Importantly, we did not consider stimulation on a single monopolar contact in the SNr area in our study design as this failed to improve segmental symptoms previously [17], and therefore is not applicable for adequate management of Parkinsonian motor symptoms.

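### The sole confirmatory endpoint is worded as a change from baseline to Visit 2, which conflicts with the three-week cross-over contrast stated elsewhere, and the reference for the two change-scores is not fixed

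*Protocol article*

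**What the plan says.** The Primary Endpoint section of the protocol article gives three statements in succession:

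- The endpoint: "The primary endpoint for the statistical evaluation will be the change in 'axial score' from baseline to visit 2 (after 6 weeks").
- The scores: "For every patient we will determine two change-scores for the two phases in the Cross-Over".
- The test: "By means of a paired t-test the null hypothesis of equality of the two therapies concerning the change in 'axial score' will be tested".

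Other sections describe the outcome differently. Outcome measures defines it as the difference in axial score "after three weeks of double-blind treatment with either" setting. The abstract places it "at three weeks of constant stimulation in either condition". The Treatment section makes Visit 1 an endpoint assessment in its own right: "After this first endpoint assessment treatment will be crossed-over and patients will be re-scheduled after further three weeks of constant stimulation".

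On the baseline itself, the Study protocol section says: "Clinical testings at baseline will be performed after overnight withdrawal of dopaminergic medication and after optimization of subthalamic stimulation". The same section puts the follow-up examinations in the dopaminergic on state. Baseline is scored under three stimulation conditions (StimOff, STNmono, STN+SNr). None of them is named as the reference for a change.

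**The concern.** Taken by itself, the endpoint sentence yields one number per patient. At Visit 2 a patient is on only one of the two settings, and the Visit 1 result on the other setting is left out. One value per patient cannot supply a paired comparison of the two therapies. It would also mix an off-medication start with an on-medication end, so it would carry the drug effect as well as any stimulation effect.

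The sentence on two change-scores moves back towards the cross-over contrast but does not say where each change starts. Two readings fit the words, and they lead to different estimates and different power.

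This is the trial's only confirmatory test, and the section says that efficacy will be claimed only on its result. The Discussion adds that the observed effect size and SD will be used to design a larger trial, so the choice of reading carries forward.

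**Working it through.** **Inputs from the Primary Endpoint section.** Difference 4.0; SD 4.0; effect size 1.0; example condition means 16.0 and 12.0; two-sided alpha 0.05; paired t-test; 10 evaluable patients plus 2 for dropout, 12 in all. Allocation to the two orders is 1:1 (Design and Methods).

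**Step 1: reproduce the plan's own figure.** Power of a paired t-test from the noncentral t distribution, with df = n - 1 and noncentrality (4.0/4.0) x sqrt(n):

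| n | Power |
|---|---|
| 9 | 74.8% |
| 10 | 80.3% |
| 12 | 88.3% |

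The stated n = 10 for 80% is reproduced. This requires 4.0 to be the SD of the within-patient differences. The sample size therefore belongs to the contrast between the two settings within each patient.

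**Step 2: notation.** Let B be the baseline score, M the three-week score on STNmono, A the three-week score on STN+SNr, d = A - M the treatment difference, and g = B - M the fall from baseline to the STNmono follow-up. Because B is taken off medication and M on medication, g includes the medication effect.

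**Step 3: the endpoint sentence alone.** The change from baseline to Visit 2 is M - B if STN+SNr came first and A - B if STNmono came first. With equal orders its mean is -g + d/2. With the example means and an assumed baseline of 20, g = 4 and d = -4, so the mean is -4 - 2 = -6. If the settings did not differ at all, it would still be -4. It does not isolate d.

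**Step 4: two changes from one common baseline.** (A - B) - (M - B) = A - M = d. The baseline cancels, the expected contrast is -4 and the power is that of Step 1. Any one of the three baseline conditions works, provided the same one serves both phases. A baseline matched to each setting would not cancel.

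**Step 5: two changes, each from the start of its own phase** (baseline to Visit 1, Visit 1 to Visit 2), taken as STN+SNr minus STNmono:

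- STN+SNr first: (A - B) - (M - A) = 2A - M - B, with mean 2d - g.
- STNmono first: (A - M) - (M - B) = A - 2M + B, with mean d + g.
- Average over equal orders: (2d - g + d + g)/2 = 1.5d, which is -6 when d = -4.

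**Step 6: spread under Step 5.** Assume independent visit errors with variance 8, so that the SD of A - M is sqrt(16) = 4. Patient effects cancel in both expressions. Within either order the variance is (4 + 1 + 1) x 8 = 48, an SD of 6.93. The two order means also differ, each lying |d - 2g|/2 from their average, which adds to the spread. The documents give no off-medication baseline mean, so it is varied:

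| Assumed baseline mean | g | Distance of each order mean from the average | Overall SD | Simulated power, n = 10 | n = 12 |
|---|---|---|---|---|---|
| 16 | 0 | 2 | sqrt(48 + 4) = 7.2 | 65% | 75% |
| 20 | 4 | 6 | sqrt(48 + 36) = 9.2 | 42% | 53% |
| 24 | 8 | 10 | sqrt(48 + 100) = 12.2 | 14% | 21% |

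Power falls below 80% even with g = 0, because the baseline and the doubled visit add error. The off/on medication gap then reduces it further. The estimate in points is too large, while the standardised effect is too small: 6/7.2 = 0.83, 6/9.2 = 0.65 and 6/12.2 = 0.49, against 1.0.

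**The case against.** The strongest defence is that the paragraph should be read as a whole. Its first sentence names a baseline, the next asks for two change-scores per patient, and the third applies a paired test of the two therapies. The natural combination is two changes from that one baseline, which is Step 4 and is correct. The test, pairing, alpha and sample size all fit it. No section calls Visit 1 a second baseline. The abstract's wording is also compatible with changes from baseline, so the clear mismatch is with Outcome measures and Treatment. Even the phase-start reading has mean zero when the settings do not differ and the orders are balanced, so it does not create an effect out of nothing.

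Most of this stands, and it limits the point. It does not remove it. The common baseline is an inference: the text gives no starting point for either change and names no baseline condition. A change-score for a phase can fairly be read as the change over that phase.

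A reader might go further and infer that the confirmatory analysis is a comparison of Visit 2 scores between the two orders, six patients against six, with far less power than stated. The documents do not support that. Two scores per patient, a paired test, a paired sample size and a first endpoint assessment at Visit 1 all exclude it.

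**Conclusion.** The point holds as a wrong and incomplete endpoint definition. It is not a fault in the test or the sample size. The phrase that fixes the endpoint at Visit 2, six weeks from baseline, contradicts Outcome measures, Treatment and the sentence that follows it. The within-patient contrast was evidently intended, and the plan is adequately sized for it if 4.0 is the SD of the paired differences.

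The consequence depends on which starting point is used. With one common baseline there is no loss. With phase-start changes the expected estimate is 1.5 times the true difference. That factor is algebraic and requires only equal numbers in the two orders and no period or carry-over effect. The power figures for that reading also rest on the assumed baseline means of 16 to 24 and on independent visit errors.

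It would overstate the case to say that the section as a whole fails to measure the cross-over effect, since one ordinary reading of it does. Because this is the only confirmatory test, the text should settle the matter before any unblinded data are seen.

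**What to change.** In the Primary Endpoint section, delete the phrase that ties the endpoint to the interval from baseline to Visit 2 at six weeks. In its place, define the primary endpoint as the axial score in the dopaminergic on state at the end of each three-week period (Visits 1 and 2), and the primary estimate as the within-patient difference [STN+SNr] minus [STNmono]. Use the same definition in the abstract and in Outcome measures.

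If the investigators prefer to keep change-scores, they should state that both are taken from one common baseline value and name the stimulation condition under which it is measured. The test and the estimate are then identical.

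The cost is a wording amendment. It needs no new visits, data or patients, and the sample size of 12 stands.
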